## 7.2

## Blinding

Individuals who conduct post-treatment (8 week and 3 month) assessments will be blinded to treatment randomization. Since treatment randomization occurs after completion of baseline measures, there is no need for blinding at baseline.

All 3 interventions are active “mindfulness” meditation interventions (i.e. no control or placebo). The only study staff that will be unblinded are the PI and the other therapist who will be delivering the treatments.

## 7.3 Reliability

Assessments will be administered by an advanced RA blind to treatment condition. [name] and I will review assessment results in weekly meetings and supervise the assessors. [name] has successfully trained and utilized advanced RAs to conduct assessments in several previous NIH-funded clinical trials of hospitalized patients with severe mood disorders. All assessors will be trained to an initial inter-rater reliability ( $>.90$ ) with periodic checks. A random sample of completed diagnostic and symptom assessments (15%) will be independently rated to determine the inter-rater reliability achieved.

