### 2.2 Specific Aims

**The primary aim of this K23 proposal is to provide hands-on training to facilitate my becoming an independent investigator in patient-oriented meditation research with an emphasis in mechanisms of action.**

Meditation, particularly mindfulness meditation, is one of the most popular Complementary and Alternative Medicine (CAM) therapies for alleviating mild-severe emotional stress, depression and anxiety and promoting wellbeing (NCCAM, 2009a; Schroevers & Brandsma, 2009). However, despite the widespread application and proliferation, numerous methodological limitations in available research preclude definitive claims about clinical effectiveness or mechanism of action (Davidson, in press; Ludwig & Kabat-Zinn, 2008; Ospina et al., 2007). At present, the largest barrier to meditation research in general, and mindfulness research in particular, is the failure to delineate meditation based-treatment packages into their most basic components and practices (Davidson, 2010)(Davidson, in press; Ospina et al., 2007).

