### **7.1.4.3 Group Randomization**

Treatment randomization is performed at the group level, rather than the individual level. For example, each group of 4-16 participants will be randomly allocated into one of three treatments (i.e. group randomization) 9 different times.

**Stratification:** Stratification by baseline characteristic will not be used because it would delay treatment, and because it is not possible in group randomization designs. Group differences in baseline characteristics will be assessed (see [Preliminary Analyses section](#))

and if present, incorporated into analysis plan under the guidance of statistical mentors. Seasonal effects will be accounted for by balancing treatment equally over the 3 seasons (spring, Summer, fall).

**Masking:** The results of each treatment randomization will be recorded and communicated by an independent RA that is not involved in patient contact.

**Procedure:** An independent statistician, [name] PhD., at Brown Center for Statistical Sciences is responsible for generating random treatment randomization sequences. The results of each randomization will be recorded by the statistician and communicated to the PI who is one of the co-therapists for each treatment. The PI will maintain the treatment location information in a password-protected electronic file, and provide de-identified codes to signify different treatments during analysis.

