### 9.5 **Treatment Randomization**

Within 1 month of the first completed baseline assessment, if at least 3 other participants have completed assessment (total of 4), proceed to randomization to choose a treatment. See Treatment Randomization for procedure.

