#### **10.1.2 Informed Consent Process:**

Written informed consent will be obtained from each subject at entry into the study. Informed consent is obtained by the following process:

1. The subject will be asked to review the study consent form.
2. The PI or Co-Investigator (Co-I) will meet with the subject to review the form, to confirm the subject's understanding of the study, and to answer any questions that the subject might have.
3. Once the subject demonstrates understanding of the study and agrees to participate in the study, the consent will be signed in the presence of eligible study staff.

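### The unblinded PI, who co-leads every treatment, supervises the IDS raters, and nothing closes a cohort before its arm is drawn

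*Protocol*

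**What the plan says.** **Masking of outcomes.** Protocol section 7.2 states: "Individuals who conduct post-treatment (8 week and 3 month) assessments will be blinded to treatment randomization". It then limits who knows the arm: "The only study staff that will be unblinded are the PI and the other therapist who will be delivering the treatments". Section 7.1.4.3 says each result is "communicated to the PI who is one of the co-therapists for each treatment", and that the PI keeps the allocation file and issues the codes used in analysis. Section 7.3 says of the PI and one colleague: "I will review assessment results in weekly meetings and supervise the assessors". The first person here is the PI, because section 2.2 describes the award as meant "to facilitate my becoming an independent investigator in patient-oriented meditation research". The safeguards in section 7.3 are a rater blind to condition, training to inter-rater reliability above .90, periodic checks, and a re-rating: "A random sample of completed diagnostic and symptom assessments (15%) will be independently rated".

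**Timing of the draw.** Section 7.1.4.2 sets a quorum of 4 eligible people with baseline complete and a latest time of 3 days before the start date. It gives no earliest time. Section 9.5 says that, within a month of the first completed baseline, "if at least 3 other participants have completed assessment (total of 4), proceed to randomization to choose a treatment". Section 5.2 plans 8 to 12 enrolled per group. Section 7.2 sees no need for baseline blinding because the draw follows baseline. On entry, section 10.1.2 says: "The PI or Co-Investigator (Co-I) will meet with the subject to review the form".

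**The concern.** A rater-scored outcome is only as well masked as the people around the rater. Section 5.3.1 lists four primary measures. DASS, PANAS and WBS are self-report, so the IDS-C30 is the one that rater blinding can protect. Under section 7.3 the raters meet weekly with, and answer to, someone who teaches the class and knows its arm. Section 7.1.3 runs one treatment at a time, so a single slip reveals the arm of the whole current cohort.

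The second risk concerns who gets in. When whole cohorts are randomised, anyone recruited or assessed after the draw may be chosen, or may choose, with the arm known to staff. The PI takes part in recruitment (section 6.8) and may conduct consent (section 10.1.2).

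Sections 11.2 and 11.4.4 expect differences between the active arms to be small, and section 11.4.1 gives estimation of treatment parameters for a later trial as the purpose. A modest bias could matter for such estimates.

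**Working it through.** **1. Outcome masking, passages side by side**

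| Fact | Section |
|---|---|
| The PI is told each allocation and co-leads each treatment | 7.1.4.3 |
| The PI is one of two staff named as unblinded | 7.2 |
| The PI reviews assessment results weekly and supervises the raters | 7.3 |
| Post-treatment raters are blind | 7.2, 7.3 |
| 15% are independently re-rated; reliability above .90 | 7.3 |

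The first three rows place an unblinded therapist over blind raters. No sentence limits the weekly review to baseline ratings or to masked material. The last row measures agreement between raters. It would not detect a bias that the raters share because the arm leaked, and the re-raters are not said to be blind or outside the PI's supervision.

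Which IDS ratings are affected? Section 9.8 schedules the IDS at 3 months. Section 7.2 mentions 8-week assessments, but the list of assessments in section 5.2 gives clinical interviews only before treatment and at 3 months. The point therefore applies at least to the 3-month IDS.

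**2. Entry after the draw**

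Inputs: quorum 4 (7.1.4.2, 9.5); planned cohort size n = 8 to 12 (5.2); 1 to 4 laboratory assessments a week (7.1.3); draw within 1 month of the first baseline (9.5).

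The protocol's own monthly yield reproduces: 4 weeks × 1 to 4 a week = 4 to 16, as section 7.1.3 states.

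Share of a cohort that could still join if the draw takes place at the quorum = (n − 4)/n:

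- n = 8: 4/8 = 50%
- n = 10: 6/10 = 60%
- n = 12: 8/12 = 67%

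Over 9 cohorts that is 9 × 4 = 36 to 9 × 8 = 72 people. With the planned 105 in 9 cohorts it is 105 − 36 = 69. These are upper bounds. If each cohort is complete when drawn, the share is 0%.

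The one-month window matters. Reaching 8 within 4 weeks needs 8/4 = 2 assessments a week, and reaching 12 needs 12/4 = 3. Section 7.1.3 allows for as few as 1 a week. At rates below these, a cohort drawn inside the window is either smaller than planned or is filled afterwards, and the protocol does not say which.

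**3. The reason given for leaving baseline unblinded**

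Section 7.2 relies on baseline preceding the draw. Sections 7.1.4.2 and 9.5 guarantee that order for 4 people per cohort. For anyone beyond the fourth it holds only if the cohort is closed at the draw, which no text states.

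**The case against.** **On outcomes.** The raters are blind, trained and spot-checked. Nothing says that scores may be changed at the weekly review or that raters are told the arm. This stands. A reader might infer that the IDS has no protection, or that the PI alters ratings, and the protocol supports neither. What remains is a conflict of roles that the stated safeguards do not address.

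**On entry.** The described order is baseline first. Section 5.2 assigns groups after baseline is complete, section 7.1.4.3 speaks of a group of 4 to 16 being allocated, and section 9.4 lists baseline before randomisation among the conditions for enrolment. Four is a minimum, tied in section 7.1.3 to very slow recruitment, and a cohort may simply be 4. This also stands: a reader might infer that late filling is planned, but no section describes a late joiner. The supportable statement is that late entry is not excluded.

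**On predictability.** Section 7.1.4.3 balances treatments over three seasons, and a reader might conclude that staff can foresee arms. If each arm runs exactly once per season over 9 cohorts, the chance of a correct guess is 1/3, 1/2 and 1 in successive years, a mean of (1/3 + 1/2 + 1)/3 = 61%, and 3 of 9 cohorts are certain. The protocol does not state that scheme. It gives nine draws as an example, and section 5.2 foresees 9 to 12 groups. The figure is conditional and the point does not rest on it.

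**On the remedy.** The PI judges whether adverse events are related (10.2.2.2), and IDS scores are scheduled adverse-event triggers (10.3.1). A blanket bar on the PI seeing ratings would conflict with those duties. This is right, and the fix must allow for it.

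**Conclusion.** The role conflict is documented: sections 7.1.4.3, 7.2 and 7.3 together give an unblinded co-therapist weekly sight of the ratings and authority over the raters. Masking of the clinician-rated IDS is weakened and not adequately protected, despite the blind rater and the 15% re-rating.

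The entry gap is one of omission. Between 0% and 67% of a planned cohort could enter after the draw. The upper end assumes a draw at the quorum of 4 and a cohort of 12. Whether any would do so cannot be told from the protocol.

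Neither limb can be turned into a shift in IDS points from the document, and the sample-size figures are untouched. The change should be made, because it concerns protocol-level roles and timing and costs little.

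**What to change.** 1. **Section 7.3.** Until data lock, a supervisor confirmed to be blind to arm and not a study therapist reviews the post-treatment and 3-month ratings and supervises the raters on them. The colleague named in section 7.3 could serve if both conditions are met; the public copy removes the name, so this needs confirming. Add an exception under which IDS safety triggers and adverse-event information reach the PI outside the rater meetings.
2. **Sections 7.1.4.2 and 9.5.** The cohort list, with eligibility, consent and baseline complete, is closed and sent to the statistician before the arm is released. Nobody joins that cohort afterwards. The reason given in section 7.2 then holds for every participant.
3. **Section 7.1.4.3.** Reconcile the two routes for communicating the allocation: an independent research assistant under Masking, and the statistician to the PI under Procedure.

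This is wording and a shift of roles, with no change to the sample size. The costs are that late volunteers wait for the next cohort, the PI has less contact with outcome data during the trial, which matters in a training award, and a separate safety channel has to be run. Closing the list does not remove any predictability that comes from seasonal balancing.

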## 8. STUDY INTERVENTIONS

MBCT is considered standard of care for treating active affective disturbances including clinically significant, mild to severe levels of depression (Barnhofer et al., 2009; [name], Haynes et al., 2010; Eisendrath et al., 2008; Finucane et al., 2006; Kenny et al., 2007; Kingston et al., 2007; Kuyken et al., 2008; Schroevers et al., 2009; Shahar et al., in press; Williams et al., 2008) and anxiety (Evans et al., 2008; Finucane et al., 2006; Schroevers et al., 2009). In this study, the two main components of MBCT (focused awareness and open monitoring) will be offered as separate 8 week modules.

### 8.1 Treatment Matching

FA/OM and MBCT interventions are matched for duration, format and content.

Classes meet for 2.5 hours once a week for 8 weeks with a daylong retreat during the 6 or 7th week. Homework consists of 45 min/day of formal meditation practice. Weeks 1-4 include practice instruction; 5-8 focus on applying the practices to manage acute negative affect.

See Appendix C for treatment manuals

## **8.2 Study Intervention Descriptions**

### **8.2.1 Intervention #1: MBCT**

MBCT ([name], Teasdale, & Williams, 2004; Z. V. [name] et al., 2002; Teasdale, 2004) is an 8-week group-based intervention that combines principles from cognitive-behavioral therapy (Beck, Rush, Shaw, & Emery, 1979) and Mindfulness-Based Stress Reduction (MBSR; (Kabat-Zinn, 1990) using a psychoeducational and client-centered format. MBCT sessions focus on cultivating mindfulness or non-judgmental present-moment awareness of mental content and everyday activities, including sitting, lying down, breathing, walking, and other simple movements. Homework assignments consisted of practicing mindfulness meditation exercises with the aid of a guided audio CD and completing worksheets related to stress, automatic thoughts, and common reactions to various types of events. A session-by session description with handouts and homework assignments is available in the MBCT manual (Z. V. [name] et al., 2002).

### **8.2.2 Intervention #2: Focused Awareness**

*Focuses Awareness Meditation (8 weeks).* The FA module will include training in focused awareness techniques which require sustained attention on a selected object (or "anchor) with concomitant deselection of surrounding objects and events. Specific practices include the body scan meditation and standard variations of breath awareness from the MBCT/SR manuals and related sources (Santorelli et al., 2003; Sekida, 1985; Wallace, 2006; Williams et al., 2007).

### **8.2.3 Intervention #3: Open Monitoring**

*Open Monitoring Meditation (8 weeks):* The OM module will include training in techniques that cultivate a non-judgmental *accepting relationship* to internal and external events, including thought and emotions, but without object selection or deselection. Specific practices include open monitoring ("choiceless awareness") meditation, mountain/ lake meditations, and labeling of mental states from the MBCT/SR manuals (Santorelli et al., 2003; [name], Williams et al., 2002; Williams et al., 2007).

## **8.3 Therapist qualifications and training**

### **8.3.1 Qualifications:**

All instructors have more than 10 years experience with mindfulness meditation, and at least 5 years of teaching experience.

### 8.3.2 Training

All instructors co-taught meditation courses with the PI and received feedback from both the PI and the participants on the clarity of their instructions and impact of the different practices.

## 8.4 Therapist Competency, Treatment Fidelity and Adherence

Creation of treatment manuals for each module is part of the K-award and will be supervised by Drs. [name], [name], [name], and [name] and other members of the Mindfulness Research Working Group. All sessions will be tape-recorded. Measures of treatment integrity will be based on multiple ratings of adherence/divergence from the treatment criteria (Jacobson et al., 1996; [name], Teasdale et al., 2002).

### 8.4.1 Adherence rating by trained judges:

Adherence will be based on variations of the MBCT adherence scale (Z V [name] et al., 2002) Competency (Crane, Kuyken, Hastings, Rothwell, & Williams, 2010), will be based on variations of the Mindfulness-Based Interventions Teaching Assessment Criteria (MBI-TAC) (Crane et al., 2011).

### 8.4.2 Ratings by Participants:

In addition to ratings from trained judges, therapists will be rated by participants according to the ***Therapeutic Factors Inventory*** (Lese & MacNair-Semands, 1996) ,***The Working Alliance Inventory*** (WAI; Horvath & Greenberg, 1989) and ***The Empathy Scale*** (ES; Burns & Auerbach, 1996)

## 8.5 Participant Compliance with Intervention(s)

### Class Attendance

### Homework Compliance:

Meditation practice logs: Participants keep track of their daily meditation practice during the 8 weeks of active treatment and follow up periods. Diaries include information about meditation practice including: a) the type of meditation (body scan, breath awareness, etc.), b) the number of minutes practiced, c) whether they fell asleep during practice d) use of CD/tape; and informal practice (walking, mindful activities). Logs for the preceding week are collected at each class meeting.

Mindfulness Skill Acquisition: The following inventories will be used to assess the degree to which the participants have acquired various mindfulness skills:

- Five Factors of Mindfulness Questionnaire (FFMQ) (Baer et al., 2006)
- The Mindful Attention Awareness Scale (MAAS) (Brown and Ryan 2004)
- Mindfulness Skill Acquisition([name] & Shahrar, 2003)

## 9. STUDY SCHEDULE

*See also Procedures Manual for Details.*

### 9.1

### Screening

Screening is a two step process and includes a phone screen and in-person interview.

#### 9.1.1 Phone screen

**exclusion criteria include:**

Current:

- age <18 or >65
- inability to read and write in English

Lifetime history of (known or diagnosed):

- bipolar disorder
- psychotic disorders (cyclothymia, schizophrenia, schizoaffective disorder)
- persistent antisocial behavior or repeated self-harm,
- borderline personality disorder,
- organic brain damage
- regular meditation practice

#### 9.1.2 In person interview

**exclusion criteria include:**

At time of screening interview (past month)

- Extremely severe levels of depression (IDS>48)
- PANAS NA <18
- active suicidal ideation (IDS-18 >2)
- presence of Axis I personality disorder
- panic disorder
- post-traumatic stress disorder
- obsessive-compulsive disorder
- eating disorder, or substance abuse/dependence
- inability to read and write in English,
- current psychotherapy ( >1 mo)
- change in antidepressant medication type or dosage in the last 8 weeks

Lifetime history exclusions:

- bipolar disorder
- psychotic disorders (cyclothymia, schizophrenia, schizoaffective disorder)
- persistent antisocial behavior or repeated self-harm,
- borderline personality disorder
- organic brain damage

#### **9.1.2.1 Concomitant Medications and Procedures**

All medication are permitted as long as there is no change within 2 months of baseline assessment or during the active phase of the study.

If the medication is psychotropic (i.e anti-depressants), changes in type or dose is prohibited duration the study. If a change in medication is warranted for safety reasons, the participant will be allowed to finish the treatment but will be considered non-compliant with protocol (i.e data not included in analysis).

Participants who are not stabilized on their (psychotropic) medications for at least 2 months may enroll later, when they have stabilized.

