### **9.9.1 Stopping Rules for an Individual Participant**

A study participant will be discontinued from further Study Intervention(s) if:

- Any clinical adverse event, laboratory abnormality, intercurrent illness, other medical condition or situation occurs such that continued participation in the study would not be in the best interest of the participant.

Development of any exclusion criteria may be cause for discontinuation.

Participant will continue to be followed with participant's permission if Study Intervention is discontinued.

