please see Procedures Manual: Manual for Managing Suicidal Ideation and Behavior and Psychiatric Hospitalization Procedures. If the study participant has experienced significant deterioration, but is not in immediate danger of hurting herself, we will take the following actions. First, we will inform the patient about procedures for contacting emergency services should they find themselves at risk for self-harm. Second, with the patient's knowledge, we will contact their primary care provider to inform them of the deterioration. We will urge the patient to make an appointment with that provider. Third, if the patient consents, we will speak with one of their family members to ensure that she is aware of the seriousness of the patient's symptoms and the agreed-upon treatment plan. We will provide psychotherapy referrals if the patient wishes them. Participants who a) require an inpatient psychiatric admission; or b) begin antidepressants or psychotherapy while in the study will be officially discontinued from the study at that point. We will collect endpoint data at the point of discontinuation. Depending on reasons for discontinuation and our clinical judgment, participants may be allowed to finish out their time in the meditation class.

Non-Response to Treatment: Independent of clinical deterioration, the possibility that the treatment will not yield benefit is another possible risk and will be explained during informed consent procedures. All patients will be monitored by study staff in person or by telephone at weekly intervals and assessed every two weeks with questionnaires about mood and affect. Non-responders (identified as minimal change in symptoms from baseline assessment) will be provided with referrals to other treatment, if desired.

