### **11.6 Missing Data**

Based on the intent-to-treat principle, all subjects allocated to treatment will be included in primary analyses, with missing data imputed as described below.

Preliminary analyses will examine patterns of missing data and drop out rates (6, 7). To minimize missing data, I will attempt to gather follow-up information even if a subject drops out of treatment. However, if these analyses show major differences between groups in attrition or missing data, various methods for imputing data (e.g., maximum likelihood estimation, “worst case” analysis) will be explored to assess the degree to which different assumptions about missingness might affect the interpretation of results (8, 9). If results are similar regardless of method used, this will increase confidence in the results obtained. In addition to these efforts to preserve missing data, sample size calculations were made with an anticipated 15% attrition rate (2, 3, 10).

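### Section 9.1.2.1 drops participants whose psychotropic medication is changed for safety reasons from the analysis, while section 11.6 keeps every allocated participant in the primary analyses

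*Protocol*

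**What the plan says.** Section 9.1.2.1 prohibits changes in the type or dose of psychotropic medication during the study and then deals with the exception: "If a change in medication is warranted for safety reasons, the participant will be allowed to finish the treatment", but that participant "will be considered non-compliant with protocol (i.e data not included in analysis". The exclusion is not limited to any particular analysis.

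Section 11.6 sets the population for the primary analyses: "Based on the intent-to-treat principle, all subjects allocated to treatment will be included in primary analyses", with missing values imputed. It adds: "I will attempt to gather follow-up information even if a subject drops out of treatment".

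Two further rules concern discontinuation. In 10.2.2.5, under adverse events, participants who need inpatient psychiatric admission, or who "begin antidepressants or psychotherapy while in the study will be officially discontinued from the study at that point", have endpoint data taken at that moment. Sections 9.9.1 and 10.5.1 say: "Participant will continue to be followed with participant's permission if Study Intervention is discontinued".

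**The concern.** A participant whose antidepressant is changed for safety in week 5 can finish the class and attend the post-treatment and 3-month assessments. Section 11.6 puts that participant in the primary analysis; 9.1.2.1 takes the data out. Whoever runs the analysis must choose, and if the choice is made after the data are in, it can be made knowing its effect on the result.

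The exclusion depends on something that happens after allocation. The example of a psychotropic drug that 9.1.2.1 gives is antidepressants, the trigger is safety, and the primary endpoint in 5.3.1 is depression, negative affect and wellbeing. A link between the trigger and the outcome is plausible, so the participants who remain may not represent those allocated.

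This matters more than the modest wording suggests. Sections 11.1 and 11.4.1 make estimation of treatment parameters for a larger trial the purpose of the study. Section 11.2 expects small differences between active arms and attaches clinical meaning to non-inferiority. A small selection bias could be comparable in size with the differences being estimated.

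**Working it through.** **Step 1: can both rules hold?**

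| Question | 9.1.2.1 | 11.6 |
|---|---|---|
| Who | Psychotropic change needed for safety | Everyone allocated to treatment |
| In the analysis? | No, without qualification | Yes, for the primary analyses |
| Completes treatment? | Allowed to | Not a condition |

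The first group is a subset of the second, so the rules give opposite answers for it. The imputation provision in 11.6 does not settle this, because these participants' scores need not be missing: they can be collected and would then be set aside.

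**Step 2: the plan's own figures.** The protocol has no figure for medication changes. Its sample size (11.4.4 to 11.4.5.1) is 90 completers at d = .335 and 105 enrolled with 15% attrition. With a noncentral F for the within-between interaction (3 groups, 2 measurements, alpha .05, and assuming a correlation of 0.5 and f = d/2), 90 completers give power 0.805. Enrolment is 90/0.85 = 105.9, against the stated 105. These figures reproduce, so the problem lies in the population definition and not in the sample size.

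**Step 3: bias within an arm.** Let a share p be excluded and let them end g SD worse than those kept. Then

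mean of all = (1 − p) × kept mean + p × (kept mean − g) = kept mean − g·p,

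so the kept mean is too favourable by g·p. Both p and g are assumptions. With g = 0.8:

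| p | 0.8p (SD) |
|---|---|
| 5% | 0.04 |
| 10% | 0.08 |
| 15% | 0.12 |
| 20% | 0.16 |

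With g = 0 there is no bias, and with g negative the sign reverses.

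**Step 4: bias between arms.** With the same g in both arms, the bias is g × (p₁ − p₂). For 10% against 20% it is 0.8 × 0.10 = 0.08 SD in size, or 0.08/0.335 = 24% of the planned d if taken on the same scale. With equal shares it is zero. If the arm that does worse loses more participants, the difference shrinks; if the better arm loses more, it widens.

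**Step 5: a second assumed mechanism.** In a simulation, benefit was normal with SD 1, and participants below a common cut-off were dropped (all of them, or half of them), with 5 to 15% lost in the better arm. That arm's mean was overstated by 0.09 to 0.27 SD. A true difference of 0.335 appeared as 0.20 to 0.29, and a true 0.20 as 0.12 to 0.17. With no true difference, the observed one stayed near zero.

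**The case against.** The strongest reply is that the statistical section states intent-to-treat explicitly, while the exclusion is a parenthesis in the screening section of a pilot that does not claim definitive significance tests. A reader would probably follow 11.6. One could also read 9.1.2.1 as setting the scores aside and imputing them under 11.6. But the protocol says neither which section prevails nor that the scores are to be imputed, and the parenthesis gives an instruction about analysis. The conflict stands, though it is easily repaired.

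Three stronger readings are tempting, and the protocol does not support them.

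- *That 9.1.2.1, 10.2.2.5 and 9.9.1 all conflict over the same participant.* The triggers in 10.2.2.5 are admission and beginning antidepressants or psychotherapy. They overlap with 9.1.2.1 only if a newly started antidepressant counts as a change. Section 10.2.2.5 also excludes nobody from analysis: "will be officially discontinued from the study at that point. We will collect endpoint data at the point of discontinuation". Section 9.9.1 applies when the intervention is discontinued, whereas a 9.1.2.1 participant may finish it.
- *That every arm's improvement is inflated.* Section 9.1.2.1 says only that the reason is safety, which could include side effects. A participant whose medication was changed could also score better by 3 months. The direction is plausible but not documented.
- *That the analysable sample falls to 77–81.* That takes an assumed 10 to 15% off the 90 completers, on top of 15% attrition. On the intent-to-treat base of 105, the same shares leave 105 × 0.90 = 94.5 or 105 × 0.85 = 89.25, around the planned 90.

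**Conclusion.** The protocol gives two incompatible answers on whether participants with a safety-driven psychotropic change are in the primary analysis. That conclusion is textual and needs no assumption. Applying 9.1.2.1 would make a post-allocation exclusion plausibly related to the primary outcome, which can bias both the within-arm and the between-arm effect sizes.

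The amount cannot be stated. The protocol gives neither the rate of such changes nor how these participants fare, and both illustrations under the working rest on assumed values. Between-arm bias can be near zero when the exclusion works alike in arms that do not truly differ.

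The discontinuation rules are a separate and weaker point. Section 10.2.2.5 takes the endpoint when the participant leaves the study, whereas 9.9.1 and 10.5.1 continue follow-up with permission after the intervention stops, and 11.6 seeks follow-up after drop-out from treatment. Leaving the study and leaving the intervention may be meant as different things, but 10.2.2.5 also allows some discontinued participants to finish the class, so the line is not clear. The gap concerns which later assessments are collected, not who is analysed.

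**What to change.** 1. In 9.1.2.1, delete the parenthesis that removes these participants' data from the analysis.
2. State there, with a reference to 11.6, that they remain in the primary intent-to-treat analysis.
3. Define a per-protocol sensitivity analysis, labelled as such, that leaves them out, and report the number left out in each arm.
4. Separately, reconcile 10.2.2.5 with 9.9.1, 10.5.1 and 11.6 on whether the post-treatment and 3-month assessments are collected after discontinuation. Which discontinuation rule should apply is for the investigators to settle and is not proposed here.

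Items 1 to 3 cost wording and an amendment, which needs IRB approval under 10.1.1. They add no visits for participants who finish treatment, because the assessments in 9.7 and 9.8 are already planned for them. The downside is that some scores in the primary analysis will include the effect of changed medication; comparison with the sensitivity analysis shows how much that matters. Item 4 may add assessments, depending on how it is resolved.
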